### Step three: seeking accommodations among stakeholders

Conceptual models built in SSM do not reflect actions of the real world [48]. In other words, activities contained in conceptual models are not to be executed identically in the real situation [48]. The models are only ‘intellectual devices’ used to further explore the situation, ‘surface’ different stakeholders’ interests and perspectives, seek accommodations among stakeholders, and learn about changes that can be made to improve the situation [50]. For this purpose, it is required to ‘compare’ conceptual models with the real situation through structured debates among stakeholders [48,50].

In this step of our study, consulting with the hospital’s chief executive and the director of the ED, we will select a diverse combination of the previously interviewed participants to hold focus group discussions. Our criteria for selection will require that the group members be well-informed about the situation. They must also be willing to cooperate and have no obstacle for participation in the group. After selecting the group members, we will hold a briefing session to make them familiar with the concepts of ‘rich picture,’ ‘purposeful activity system,’ ‘root definition,’ ‘CATWOE,’ and ‘conceptual model,’ and how we are going to use them. The briefing session will be held in the hospital, and is estimated to last about one hour. Then, we will schedule focus group meetings and invite partcipants accordingly. If it will not be possible for a patient to attend the meetings, one of the researchers will play his/her role instead. We will use a guide to conduct the meetings. Group discussions will be focused on comparing the ‘conceptual models’ (*i.e.*, the insightful propositions for improving the quality of care) with the ‘rich picture’ (*i.e.*, the perceived situation regarding quality of care). To carry out the comparison, we will present the rich picture and one of the conceptual models to the participants and start asking some questions: ‘Is the proposed conceptual model relevant to the situation?,’ ‘Do the activities of the conceptual model ever take place in the real situation?,’ ‘How are they performed?,’ ‘How do you—participants—judge those activities?,’ ‘What can be really done to improve the situation?’ In order to more explore the situation and clarify participants’ viewpoints, we will continue by asking follow-up and probing questions [50]. It is estimated that each meeting will last about two hours. All conversations will be digitally recorded by permission. Short notes will be taken during discussions and completed soon after the meetings. We will also download and transcribe the recorded files.

During the debates, the participants’ views on ‘quality-of-care issues’ and ‘changes that may improve the quality of care’ will be further explored. Therefore, based on the participants’ accommodations, it will become apparent whether a given conceptual model and its included activities are really ‘relevant’ to the situation and can lead to finding changes. If the debate does not reach to an accommodation among participants, we will propose other conceptual models (previously built or to be built) in subsequent meetings. To build new conceptual models, we will analyze the data collected from the meetings, as was stated above (in ‘construction of meaning’). Newer themes will be constructed by continuous comparing of the emergent themes with the original ones. This process can lead to the modification of the rich picture, the emergence of newer relevant systems, and the formation of newer conceptual models.

For the purpose of this step to be achieved, the mentioned cyclic process may be repeated several times [48,50]. Therefore, we cannot determine the number of focus group meetings. Nevertheless, based on the very complexity of the problem situation in this study, we think there will not be less than five or six meetings.

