### Interview with key stakeholders

We will conduct semi-structured interviews with key stakeholders regarding the quality of care. Interviewees will be selected purposefully from among the hospital’s chief executive and his assistants, the general manager, the matron, supervisor nurses, the director of the ED, attending physicians, emergency nurses, residents, patients, and the people who accompany patients in the ED. We estimate that there will be approximately 40 diverse interviews. Purposeful sampling of interviewees will be started with typical case sampling and continued with snowball sampling, considering the maximum diversity. To obtain a comprehensive account of the situation, we will also use other sampling strategies, such as ‘emergent sampling,’ selecting ‘confirming and disconfirming cases,’ and selecting ‘politically important cases’ [52]. All participants will be informed about the study objectives and methods (*e.g.*, digital recording of interviews), and our ethical policy of voluntary participation and participants’ confidentiality. They will be asked to fill a consent form prior to the interviews. The interviews will be conducted according to an interview guide at an agreed time and preferably in the hospital (see the interview guide in Additional file 2). It is estimated that each interview last about one hour. We will digitally record all of the interviews after participants’ permission. All recorded interviews will be downloaded, labeled, and transcribed verbatim immediately. We may also take some handwritten notes during interviews.

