### Step two: providing relevant ‘purposeful activity models’

Checkland believes that, in any given problem situation, there are various stakeholders with different worldviews, interests, and purposes [40]. Grounded on these different individual properties that are unique to a particular situation, each stakeholder assumes performing a definite set of ‘purposeful activities’ will achieve a specific goal and also improve the situation [48]. In SSM, these notional sets of human purposeful activities are used to build ‘conceptual models’ that are ‘relevant’ to the situation [50]. Based on the perceived situation, SSM user should ‘select’ several relevant sets of human purposeful activities [48]. To build the conceptual models, each selected notion should be clearly described by a ‘root definition’ and a ‘CATWOE’^a^[48]. A ‘conceptual model’ is then built accordingly [48,50]. Conceptual models must have the characteristic properties of a ‘system’ (*i.e.*, hierarchical structure, emergent properties, communication, and control) [48,50]. Thus, each conceptual model should consist of some (usually five to nine) activities that are dependent upon each other, definition of measures of performance for the notional system, and monitor and control activities [48,50].

In this study, according to the above instructions, we will build some conceptual models. Since the themes and subthemes (that emerge in step one) represent ‘quality-of-care issues’ and ‘relevant actions and processes that construct those issues,’ we will insightfully use them to select and describe relevant sets of purposeful activities and build conceptual models. According to Checkland, ‘no human activity system is intrinsically relevant to any problem situation’ [48]; therefore, although our conceptual models will be grounded in real world data, these models will be just insightful propositions for improving the quality of care, which should be tested among the study participants. In this regard, to achieve the purpose of modeling (in the next step), we will try to build a number of conceptual models. Because we will be focused on CG for quality improvement in the selected ED, all of our conceptual models will be subsumed under the rubric of ‘the relevant models of CG.’

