### Step four: defining changes to improve the quality of care

The final purpose of the focus group discussions is to find changes that, from the perspectives of the participants, are ‘desirable’ regarding improvement of the quality of care, and ‘feasible’ concerning the current culture. During the debates, the participants’ worldviews will be contrasted with each other, so that accommodations can be made on what will be a change to improve the quality of care. Changes may be about structures, processes, and attitudes [48,50]. As stated above, we will seek accommodations among stakeholders on which conceptual model and its included activities are really ‘relevant’ to the situation. Then, it will become possible to find changes through the process of ‘comparison.’ During this process, our criterion for defining changes is participants’ agreement with suggested change statements. We will then take those statements as defined changes to improve the quality of care in the selected ED.

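### A researcher may play an absent patient in the focus groups, and nothing stated keeps that contribution out of the analysis or the agreement that defines a change

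*Protocol article*

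**What the plan says.** All references are to the protocol article, Methods/design.

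- **Who sits in the groups (Step three).** "we will select a diverse combination of the previously interviewed participants to hold focus group discussions". Members must know the situation well, and "They must also be willing to cooperate and have no obstacle for participation in the group". The hospital's chief executive and the ED director are consulted on the selection.
- **What happens if a patient cannot come (Step three).** "If it will not be possible for a patient to attend the meetings, one of the researchers will play his/her role instead".
- **What is debated (Step two).** The research team builds the conceptual models. The article says of them: "these models will be just insightful propositions for improving the quality of care, which should be tested among the study participants".
- **What is done with the meetings (Step three).** The team presents the models and asks the questions. Conversations are recorded with permission and transcribed. If a debate reaches no accommodation, the meeting data are analysed to build new models, and this can change the themes and the rich picture.
- **What counts as a result (Step four).** The purpose is stated as: "The final purpose of the focus group discussions is to find changes that, from the perspectives of the participants, are" desirable and culturally feasible. The rule is: "our criterion for defining changes is participants’ agreement with suggested change statements". Statements agreed in this way become the defined changes.
- **Where patients otherwise appear (Interview with key stakeholders).** The step-one interview pool includes "emergency nurses, residents, patients, and the people who accompany patients in the ED".
- **What is member-checked (Construction of meaning).** The emergent themes and the rich picture, repeatedly during the study.

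**The concern.** The focus groups are where the study tests its own models and settles its output. A test among participants is informative only if the people judging the models are not the people who built them. The role-play rule lets one of the builders take the patient's place in that judgement.

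The section on the conceptual framework treats quality of care as something constructed from the value judgements of stakeholders, and step four relies on their worldviews being contrasted with each other. A researcher's rendering of a patient is not a patient's value judgement, however well informed it is. The Background lists patient and public involvement among the pillars of clinical governance, so this is a poor stakeholder group to simulate.

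At stake is what the defined changes can be said to represent. A change could be described as agreed among stakeholders, with the patient side apparently covered, when no patient had seen the statement.

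**Working it through.** The plan has no figure to reproduce on this point, and the conclusion depends on no calculation. The check is to follow the rule through the steps and ask at each one whether the text separates the stand-in from the participants.

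1. **Entry.** Step three admits a researcher in the patient's role when a patient cannot attend. The wording could mean one invited patient or any patient, and one meeting or the whole series. The point applies under each reading.
2. **Independence from the models.** Step two makes the research team the authors of the models and says the models should be tested among participants. The stand-in is drawn from that team. The two provisions sit badly together, though they do not contradict each other outright.
3. **Recording.** Step three records and transcribes the conversations. No sentence says that speech in the patient's role is labelled or left out.
4. **Analysis.** Step three sends meeting data back through the thematic analysis when new models are needed. No sentence excludes the stand-in's speech there either.
5. **Agreement.** Step four states one criterion, participants' agreement. It does not say whether a researcher in role is a participant for this purpose.
6. **Grounding.** The rule does not require the role to be based on the patient interviews.
7. **Later check by patients.** Member checking is stated for the themes and the rich picture. It is not stated for the change statements, which are the product of step four.

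**How often the rule could apply.** The article expects at least five or six meetings of about two hours, plus a briefing of about one hour. The time asked of a member is therefore at least about 5 × 2 + 1 = 11 to 6 × 2 + 1 = 13 hours. Members must also have no obstacle to taking part. The article does not say how likely a patient is to meet these conditions, so no rate can be given. It sets no minimum number of meetings with a real patient present, so a stand-in at every meeting is permitted.

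**Patient-side input that remains.** Patients and accompanying persons can be interviewed in step one, and those interviews feed the themes and the rich picture against which each model is compared. Interviewed accompanying persons are also eligible for the groups. The gap is therefore in the debates and in the agreement on changes, not in the whole study.

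**The case against.** The strongest defence is that the article never says the stand-in counts. Group members are drawn from people already interviewed, and the criterion is the agreement of participants. A researcher is neither, so a plain reading can leave the stand-in out. This stands in part: it rules out saying that the plan counts the researcher's voice. It does not settle the matter, because the same sentence puts the researcher in the patient's place and no sentence then separates the two.

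Other points carry weight:

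- The rule is an openly stated fallback. Real patient views reach the study in step one, and repeated member checking would extend to later revisions of the themes and rich picture. This limits the gap but does not reach the change statements.
- The models are described as devices for inquiry, to be replaced if no accommodation is found, so the design does not depend on any one of them being accepted. This weakens the conflict of interest but does not remove it.
- The planned journal covers how the focus groups are conducted and how accommodations are found, so use of a stand-in would probably be recorded. A record makes the problem visible but does not keep the contribution out of the agreement.
- The meeting guide and the unspecified rigour strategies may say more. The point rests on a rule the article states, not on detail it leaves out.

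A reader might also infer something stronger: that the study will contain fabricated patient data, or that a researcher holds a fixed share of the votes or a veto. The documents support none of this. Nothing indicates that invented input would be passed off as coming from patients. The article gives no group size, does not define agreement as unanimity, and seeks accommodation rather than a vote.

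**Conclusion.** The concern holds in a limited form. As written, a member of the team that builds the models may speak for the patient in the debates that test them. Nothing stated keeps that contribution out of the transcripts, the step-three analysis or the agreement, which is the only stated criterion for a defined change. The patient perspective at that stage could therefore be simulated by the researchers.

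This rests on reading the article's silence as leaving the matter open, not as a rule that the stand-in counts. It also assumes that the unseen meeting guide does not already deal with it.

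The weakness is moderate. It involves no numerical error and no direct contradiction, it leaves step one intact, and the study ends at defining changes after one cycle. It is still worth correcting before the focus groups, because it bears on the study's main product and the correction is cheap.

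**What to change.** Replace the role-play sentence in Step three with an order of substitution and a rule on data:

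1. Offer an absent patient's seat first to another interviewed patient or to an interviewed accompanying person. Both are already in the interview pool.
2. If none can attend, use anonymised extracts from the patient interviews to prompt the discussion.
3. Label any researcher speech in the transcripts. Exclude it from participant data and from the agreement criterion in Step four.
4. Extend the existing member checking to the draft change statements, with a few interviewed patients or companions.
5. Report any change that none of them reviewed as not patient-reviewed.

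The cost is a short protocol edit and a few brief contacts with people already interviewed. The downside is that some changes may have to be reported without patient endorsement, which would describe accurately how they were reached.

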### Step four: defining changes to improve the quality of care

The final purpose of the focus group discussions is to find changes that, from the perspectives of the participants, are ‘desirable’ regarding improvement of the quality of care, and ‘feasible’ concerning the current culture. During the debates, the participants’ worldviews will be contrasted with each other, so that accommodations can be made on what will be a change to improve the quality of care. Changes may be about structures, processes, and attitudes [48,50]. As stated above, we will seek accommodations among stakeholders on which conceptual model and its included activities are really ‘relevant’ to the situation. Then, it will become possible to find changes through the process of ‘comparison.’ During this process, our criterion for defining changes is participants’ agreement with suggested change statements. We will then take those statements as defined changes to improve the quality of care in the selected ED.

### Reflecting on the study as a whole

As stated earlier, the overarching purpose of this study is to understand how CG can be defined and implemented in an ED. We considered ‘CG implementation in an ED’ as a complex problem situation. Therefore, assuming SSM as a useful methodology in approaching this kind of situations, we used it to design the process of our action research study and inquire into its content. We conceptualized CG as a set of purposeful activities. We assumed implementing that set of purposeful activities (*i.e.*, the conceptualized CG) as our study steps will yield two results: the quality situation of the selected ED will be explored; and the changes to improve the quality of care in the selected ED will be found.

During this action research, we will learn about CG and its implementation in the selected setting, through critical reflection on our assumptions [49]. In this regard, we will keep a descriptive journal of different aspects of the study, including how the sources of data will be selected; how data will be collected; what data will be collected; how data will be analyzed and interpreted; how conceptual models will be built; how conceptual models will be used; how focus group discussions will be conducted; how accommodations will be found; what influencing events will occur; and what contextual factors we will face. Reviewing the journal, we will also write analytic memos throughout the research process. We will use some sensitizing concepts to guide our memos, including complexity of quality improvement in the ED; accountability toward improving the quality of care in the ED; efficacy of SSM and the methods used in achieving our objectives; problems and obstacles to the implementation of the study steps; and modifications that need to be made to the study methods and processes. As memos develop over time, new hypotheses will be formed. This will lead to further thinking, searching for approving or disapproving data, and further memos [53]. Finally, putting the memos in the context, we will develop the emergent understanding of the whole study by narrative synthesis of the memos.

### Ethical considerations

Ethics approval for this study was obtained from the Ethics Committee of TUMS. In order to gain access to the setting, the research team will follow all necessary legal procedures. We will obtain the letter of introduction from the hospital’s chief executive and provide it to the relevant authorities. Researchers will respect all stakeholders and their right to voluntarily participate in the study. All participants will be informed about the objectives of each study step, methods of participation, methods of data collection (*e.g.*, digital recording of interviews and discussions), and protected confidentiality of the participants. We will ask them to fill a consent form prior to interviews and focus group discussions. We will also obtain necessary permissions for all field observation sessions.

## Discussion

In the late 1990s, the England’s Department of Health introduced ‘clinical governance’ as a framework to make healthcare organizations ‘accountable for continuously improving the quality of their services’ [21]. The new framework was based on the NHS specific history, context, and conditions [23]. At that time, considering the underlying issues, CG was conceptualized as the ‘seven pillars’ standing on the ‘five solid foundations’ [23]. In 2009, the implementation of CG became mandatory for all hospitals in Iran. However, Iranian hospitals work in a different context. Therefore, it is expected that these organizations will face different governance issues in their way toward quality improvement.

In spite of the assumed similarities in decision-making processes in different countries, it is advocated that each country should consider its specific underlying situation in planning for the quality improvement [55]. Implementation of CG is subject to the same condition [56]. CG is a complex, dynamic, and strategic framework that requires a comprehensive understanding of existing issues in order to identify and facilitate appropriate processes for being effectively implemented [57,58]. Taking these issues into account, it seems that the mere dissemination of the seven pillars of CG and some initiatives will not necessarily result in a successful CG implementation in Iranian hospitals. It is essential to develop comprehensive interventions to drive substantial changes [59,60].

In recent years, systems approaches have been more advocated in health areas due to the need for better understanding of influential factors in healthcare environment and overcoming health systems’ complexities [55,61-63]. But they are different in underlying assumptions, methodologies, and practical methods [38]. According to the ‘hard’ systems paradigm, the idea of CG can be captured in a model such as the ‘seven pillars’ model. Thus, CG implementation would focus on interventions that aim to strengthen the seven pillars in order to optimize ‘the system’ and improve the quality of care. In contrast, based on the ‘soft’ systems perspective, CG and quality improvement in a selected healthcare setting is a problem situation that requires to be explored in order to find relevant issues and appropriate interventions; thus, initially, no *a priori* model of CG is regarded as suitable for the given situation.

Using SSM as a problem structuring approach, we will do this action research as a vehicle to understand CG and how it can be implemented in the selected ED. We will record all events and research processes thoroughly, including how we will overcome obstacles in each study step. Thus, reflections on involvement in this study will make it possible to explain the following subjects in the selected ED: What issues need to be governed in order to improve the quality of care; what CG means; how CG can be implemented; and how SSM can be used to facilitate the implementation of CG.

It has been noted that description of contexts and operational challenges in quality improvement projects has a profound effect on the development of implementation science and the related initiatives [64]. Therefore, we intend to disseminate the results of this study focusing on ‘a thick description of contexts and complexities’ of quality improvement through CG implementation in the selected setting. The results can also be instructive for, and employed by, boards and executives governing other clinical settings to facilitate CG implementation.

This is also the first study in Iran’s health system that uses SSM as the guiding methodology. We anticipate that some issues regarding the organization’s culture (*e.g.*, teamwork, open communication, and power relations due to professionalism) will be among our study challenges. Nevertheless, the researchers’ experience in qualitative methods, along with flexible use of SSM and its relevant ‘intellectual devices’ will help us overcome those challenges. Moreover, we hold the support of the management team in the selected ED.

